## Abstract

**Context:**

While oral immunotherapy (OIT) has been shown to promote the remission of mild peanut allergy in young children, there is still an unmet need for a disease-modifying intervention for older patients and those with severe diseases. In mice models, abatacept, a cytotoxic T lymphocyte-associated antigen-4 (CTLA-4) immunoglobulin fusion protein, has been shown to promote immune tolerance to food when used as an adjuvant to allergen immunotherapy. The goal of this study is to explore the potential efficacy of abatacept in promoting immune tolerance to food allergens during OIT in humans.

**Methods:**

In this phase 2a proof-of-concept study (NCT04872218), 14 peanut-allergic participants aged from 14 to 55 years will be randomized at a 1:1 ratio to abatacept vs. placebo for the first 24 weeks of a peanut OIT treatment (target maintenance dose of 300 mg peanut protein). The primary outcome will be the suppression of the OIT-induced surge in peanut-specific IgE/total IgE at 24 weeks, relative to the baseline. Sustained unresponsiveness will be assessed as a secondary outcome starting at 36 weeks by observing incremental periods of peanut avoidance followed by oral food challenges.

**Discussion:**

This is the first study assessing the use of abatacept as an adjuvant to allergen immunotherapy in humans. As observed in preclinical studies, the ability of abatacept to modulate the peanut-specific immune response during OIT will serve as a proxy outcome for the development of clinical tolerance, given the small sample size. The study will also test a new patient-oriented approach to sustained tolerance testing in randomized controlled trials.

## 1. Introduction

### 1.1. Context of the study

Oral immunotherapy (OIT) is a new treatment for food allergy (FA) (1). It consists of the regular ingestions of the allergen in a medically supervised manner to achieve a state of desensitization, defined as an increase in the patient's reactivity threshold while on therapy. Desensitization can be achieved in most patients with success rates ranging from 60 to 100% (2–6). It offers protection from accidental ingestion and improvement in quality of life (7). Over time, OIT can also lead to clinical remission, which is defined as a lack of clinical reaction to a food allergen after active therapy has been discontinued, thus indicating a modification of the underlying disease (8). It is more likely to be achieved in younger children with low levels of food-specific immunoglobulin E (IgE) and is seldom observed after the age of 9 years (9, 10). In other words, OIT appears to have a limited ability to induce oral tolerance once immune memory has been firmly established. Thus, there is an unmet need for an intervention that can target the patient's immune memory to the allergen.

### 1.2. Memory reactivation during OIT

FA memory is mediated by B and T memory cells in lymphoid organs as well as by long-lived IgE-producing plasma cells that can persist for years in the bone marrow (11–13).

During the early phase of OIT, exposure to the allergen results in the reactivation of memory B cells that are dependent on type-2 memory T cells (Th2 cells) (14), which leads to the generation of new IgE-producing plasma cells and the expansion of the allergen-specific B-cell repertoire through somatic hypermutation (15). This phenomenon is reflected in the 1st month of therapy by a sudden rise in allergen-specific IgE (sIgE) (16). The intensity of the sIgE surge has been shown to inversely correlate with the likelihood of developing clinical remission, further suggesting its value as a proxy measure for immune memory reactivation (9, 17). Clinical remission is also typically associated with allergen-specific T-cell transition from a type 2 phenotype to one of immune regulation or exhaustion (18).

### 1.3. Effect of CTLA-4 and abatacept on T cells and plasma cells

Abatacept is a cytotoxic T lymphocyte-associated antigen (CTLA-4)-immunoglobulin fusion protein approved by the U.S. Food and Drug Administration (FDA) and Health Canada for adults with psoriasis and rheumatoid arthritis as well as for children of 6 years and older with juvenile idiopathic arthritis. Abatacept interferes with the delivery of the costimulatory signal required for T-cell activation and plasma cell survival (19).

T cells require two distinct signals from antigen-presenting cells (APCs) in order to activate (20). The first signal is delivered to the T-cell receptor (TCR) by a major histocompatibility complex (MHC) carrying the antigen and is responsible for immune specificity. The second signal is mediated by co-stimulatory receptors, which validate that an immune response should indeed be mounted against that antigen. It is delivered by B7 proteins (CD80/CD86) on activated APCs to the CD28 receptor on T cells (21). The simultaneous delivery of both signals triggers T-cell proliferation, survival, and activation. Conversely, TCR engagement in the absence of a co-stimulatory signal (e.g., from non-activated APCs) results in T-cell anergy or apoptosis (Figure 1) (22).

**Figure 1 F1:**
[figure not shown]
Second signal blockade in T cells. APC, antigen-presenting cell; CTLA-4, cytotoxic T lymphocyte-associated antigen-4; MHC, major histocompatibility complex; TCR, T-cell receptor.

CTLA-4 is a regulatory receptor naturally expressed by T cells in the days following their activation. It has a much higher affinity for B7 molecules than CD28 and dislodges it in a competitive manner (23). CTLA-4 interrupts the second signal and activates regulatory signals that serve as a homeostatic negative feedback mechanism to downregulate B and T-cell activation (19, 24). The goal of abatacept is to sequester B7 molecules prior to T-cell activation and prevent the delivery of the second signal.

The concept of first and second signals also applies to some extent to IgE-producing plasma cells. Contrarily to IgG-producing plasma cells, IgE-producing plasma cells retain a functional BCR after differentiation (25), and it was recently shown that binding their antigen induces apoptosis in a dose-dependent manner (26). Plasma cells are rescued from this antigen-dependent apoptosis by CD28-induced transgene, Bcl-2 (27). Plasma cells (contrarily to B cells) express CD28, which interacts with B7 molecules on bone marrow stromal cells to prevent apoptosis (27). If abatacept was co-administered along with the antigen, B7 sequestering would be expected to prevent stromal cells from rescuing antigen-specific IgE-producing plasma cells and lead to their selective deletion (Figure 2).

**Figure 2 F2:**
[figure not shown]
Second signal blockade in IgE^+^ long-lived plasma cells. Ag, antigen; APC, antigen-presenting cell; BM, bone marrow; Cas3, caspase-3; DC, dendritic cell; LLPC, long-lived plasma cell; MHC, major histocompatibility complex; TCR, T-cell receptor.

### 1.4. Effect of CTLA-4 and abatacept on the allergic response

Genetic association studies have hinted at a link between CTLA-4 and allergic disease for some time. In 2004, four single nucleotide polymorphisms of CTLA-4 were found to be associated with IgE production and allergic phenotype in a cohort of 364 asthmatic families from European countries (28). The results were later confirmed in a meta-analysis regrouping 6,378 cases of asthma and 8,674 controls (29).

In 2013, a randomized controlled trial in adults with mild asthma failed to show the superiority of a 3-month treatment with abatacept over placebo at decreasing eosinophilic inflammation on subsequent allergen-specific bronchial challenges. This led the authors to conclude a lack of efficacy of second signal blockade in allergic inflammation (30). However, the study had a fundamental limitation, in that the subjects were not exposed to their allergen during the treatment phase. The results simply confirm that in the absence of the first signal, it is futile to block the second signal (immunological ignorance) (31). In auto-immune disease and transplantation, the antigen is expressed constitutively by the organism or the graft. On the other hand, allergic patients usually do their best to avoid contact with their allergen. The only way by which abatacept would be expected to exert an immunomodulatory effect in allergic disease would be if it was co-administered with the allergen.

Van Wijk et al. reported, in 2007, that abatacept completely prevented primary humoral (IgE and IgG) and cellular [interleukins (IL)-4 and 5] sensitization to peanut in mice when added to cholera toxin-based oral sensitization protocol (32). Allergic sensitization could also be prevented by pre-treatment with peanut alone prior to the oral sensitization protocol, assumedly due to the development of a primary regulatory response. Blockade of CTLA-4 during this peanut pre-treatment completely abrogated this protective effect, while blockade of IL-10 or TGF-β did not (32). Similarly, Krempski et al. recently reported that CTLA-4 blockade prevents the development of oral tolerance to peanut butter in mice (33).

Several groups reported improvements in airway eosinophil infiltration, IgE production, type-2 cytokine release, and allergen-specific airway hyper-reactivity in mice following treatment with abatacept (34–37). All animals in these studies were exposed to the allergen at some point while receiving the drug. In 2013, Maazi et al. explored the effect of combining abatacept with subcutaneous immunotherapy (SCIT) in mice sensitized to ovalbumin (38). Mice in the SCIT + abatacept treatment group had a significant improvement in allergen-induced airway hyper-reactivity, airway eosinophilia, and serum ovalbumin sIgE levels compared with mice on SCIT alone (38). Importantly, these outcomes were measured after 20 days of treatment discontinuation and thus represented sustained changes.

### 1.5. General hypothesis

We hypothesize that in teenagers and adults with persistent severe peanut allergy, administering peanut antigen through OIT while simultaneously blocking the second signal with abatacept will prevent the reactivation of the secondary allergic immune response and selectively suppress peanut-specific memory T and IgE-producing plasma cells, and thereby improve the rates of clinical remission.

The ATARI trial is a phase 2a proof-of-concept trial comparing the efficacy of abatacept vs. placebo at suppressing the sIgE surge in the 1st month of peanut OIT, treated as a proxy measure of immune memory reactivation.

## 2. Methods and analysis

### 2.1. Design

This study is a phase 2a, double-blinded, and randomized proof-of-concept trial comparing abatacept with placebo as an adjuvant to OIT in peanut-allergic adolescents and adults. The study will be conducted in Sainte-Justine Hospital (Montreal, Quebec, Canada). A total of 14 patients will be recruited and randomized 1:1 to receive abatacept or placebo (normal saline solution), in association with a peanut OIT for 24 weeks, after which OIT will be continued alone (Figure 3).

**Figure 3 F3:**

ATARI study design. OIT, oral immunotherapy; OFC, oral food challenge. *Corresponds to the serologic tests.

Starting at week 36, participants will undergo a series of up to five oral food challenges (OFCs), interlaced with incremental periods of avoidance over 12 weeks to characterize the extent of sustained unresponsiveness (SU) to peanut (Figure 3).

### 2.2. Study outcomes

The primary outcome of the trial is the relative change from baseline in peanut-specific/total IgE ratio at the end of the treatment phase (week 24). The use of the specific/total IgE ratio aims to control for non-specific fluctuations in IgE production.

Secondary outcomes include the following:

The relative change in peanut-specific IgG4/IgE (sIgG4/sIgE) ratio from baseline to week 24.The absolute change in peanut sIgG4 from baseline to week 24.The maximum period of avoidance after which an OFC with 300 mg peanut protein is still tolerated.The mean cumulative function of food dosing allergic reactions.The highest tolerated dose on week 36 OFC.The time from the onset of OIT to the maintenance dose of 300 mg.The overall rate of adverse events (AEs).

Exploratory outcomes include the following:

a. Change in peanut atopy patch test from baseline to weeks 12, 24, and 48.b. Change in peanut skin test from baseline to weeks 12, 24, and 48.c. Relative change in peanut-specific/total IgE from baseline to weeks 2, 6, 12, 36, and 48.d. Relative change in peanut sIgG4/sIgE ratio from baseline to weeks 2, 6, 12, 36, and 48.e. Absolute change from baseline in peanut sIgG4 to weeks 2, 6, 12, 36, and 48.f. The highest tolerated dose on week 38 OFC [72 h SU].g. The highest tolerated dose on week 40 OFC [1-week SU].h. The highest tolerated dose on week 43 OFC [2-week SU].i. The highest tolerated dose on week 48 OFC [4-week SU].

### 2.3. Selection of participants

The study aims to enroll 14 participants aged 14–50 years with serum peanut sIgE >50 kU/L. The inclusion and exclusion criteria are presented in Tables 1, 2, respectively. For female participants of child-bearing potential, a urine pregnancy test will be conducted on randomization day. Since asthma is an important concern when initiating OIT, a focus on uncontrolled asthma should be made. Criteria for uncontrolled asthma are as follows:

- History of two or more systemic corticosteroid courses within 6 months of screening or 1 course of systemic corticosteroids within 3 months of screening to treat asthma/wheezing;- One hospitalization or emergency department visit for asthma/wheezing within 6 months of screening;- Forced expiratory volume in 1 s (FEV1) <80% of predicted or FEV1/forced vital capacity (FVC) <75%, with or without controller medications;- Inhaled corticosteroid dosing of >500 mcg daily fluticasone (or equivalent).

**Table 1 T1:** Inclusion criteria.

1. Male or female participants 14–50 years old at screening visit.
2. History of IgE-mediated allergy to peanut protein.
3. Peanut-specific IgE level >50 kU/L.
4. Total IgE level <5,000 kU/L.
5. Willing to comply with all study requirements during participation in the study.
6. Signed informed consent and assent.

**Table 2 T2:** Exclusion criteria.

1. Previous adverse reactions to abatacept.
2. Known hypersensitivity to abatacept or any of its components.
3. Patients at risk of sepsis, such as immunocompromised or HIV positive.
4. Patient undergoing treatment with any other biologic agent.
5. Partly controlled or uncontrolled asthma, as defined by GINA 2020.
6. Unstable angina, significant arrhythmia, uncontrolled hypertension, chronic sinusitis, or other chronic or immunological diseases that, in the judgment of the investigator, might interfere with the evaluation, administration of the test drug, or pose additional risk to the subject (e.g., gastrointestinal or gastroesophageal disease, chronic infections, scleroderma, hepatic and gallbladder disease, and chronic non-allergic pulmonary disease).
7. Current users of oral, intramuscular, or intravenous corticosteroids, tricyclic antidepressants, or beta-blocker.
8. Concurrent/prior use of immunomodulatory therapy (within 6 months), including allergen-specific immunotherapy.
9. A diagnosis of eosinophilic esophagitis, eosinophilic colitis, or eosinophilic gastritis.
10. Pregnant or breastfeeding women.
11. Chronic or latent infections with Hepatitis B, Hepatitis C, or tuberculosis.
12. Active infection.
13. Chronic Obstructive Pulmonary Disease (COPD).
14. Expected need for live vaccination during the course of the study.
15. Known malignancy.

Several study requirements will also be verified before inclusion as follows:

- Participants should be willing to be trained on the proper use of an epinephrine autoinjector and willing to possess an epinephrine autoinjector for the duration of the study or similar.- Participants should be able to discontinue their usual anti-allergic medication prior to skin prick tests and/or OFC, as described in Section 3.7.- Female participants with childbearing potential must agree to remain abstinent (refrain from heterosexual intercourse) or use acceptable contraceptive methods (i.e., barrier methods or oral, injected, or implanted hormonal methods of contraception or other forms of hormonal contraception that have comparable efficacy) during the trial.

### 2.4. Study drug

The first three doses of abatacept vs. placebo will be separated by an interval of 2 weeks, while the remaining doses will be given monthly, as recommended for autoimmune disorders. Since participants will be aged 14 years and older, adult dosages will be used, based on the participant's body weight: 500 mg if body weight < 60 kg, 750 mg if body weight ranges between 60 and 100 kg, and 1,000 mg if body weight > 100 kg.

The randomization list will be generated by the study pharmacist using simple randomization. The medication or placebo will be transferred into a generic IV bag to maintain blinding and identified with the participant's ID and a blinded investigational product label. It will be administered intravenously through a 0.2–1.2 μm low protein-binding filter over 30 min by the blinded study nurse, as recommended by the abatacept product monograph. Since the study drug contains maltose and the placebo does not, to ensure the blinding in participants with diabetes, glycemia will not be monitored for 4 h following the perfusion.

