### 2.9. Statistical considerations

Based on observations from preclinical studies in mice, abatacept is expected to suppress the allergen-specific IgE surge induced by OIT. The relative change in specific/total IgE at 24 weeks will be compared between the two groups using Student's *t*-test. A 50% suppression was deemed clinically significant.

Based on the PALISADE trial (6), we expect the placebo group (OIT alone) to increase their specific IgE levels by 100% with a standard deviation of <30%. Based on this assumption, a sample size of 12 participants with a 1:1 randomization ratio would allow the detection of a 50% difference in the increase in sIgE, with an alpha risk of 0.05 and a power of 80%. A total sample size of 14 patients would allow to account for 15% of lost follow-up.

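### Simple randomization of 14 participants does not secure the 1:1 split used in the sample-size calculation; a restricted list closing at 7:7 is a cheap, recommended improvement

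*Protocol article*

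**What the plan says.** Three places in the protocol article bear on this.

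- Section 2.4 (Study drug), on the method: "The randomization list will be generated by the study pharmacist using simple randomization". It mentions no blocking, stratification or forced total, and neither does any other section.
- Section 2.1 (Design), on the allocation: "A total of 14 patients will be recruited and randomized 1:1 to receive abatacept or placebo".
- Section 2.9 (Statistical considerations), on the sample size: "a sample size of 12 participants with a 1:1 randomization ratio would allow the detection of a 50% difference in the increase in sIgE". The control arm is expected to rise by 100% with an SD below 30%, alpha is 0.05 and power is 80%. On attrition: "A total sample size of 14 patients would allow to account for 15% of lost follow-up".

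The primary test in section 2.9 is Student's t-test on the relative change in the specific/total IgE ratio at week 24.

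**The concern.** Simple randomization is, by its usual definition, an independent draw for each participant with no constraint on the totals. In a large trial the arms come out nearly equal anyway. With 14 participants they often do not, while the sample-size calculation assumes equal arms.

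Two things are at stake. First, for a given total, unequal arms give a less precise difference in means, and power margins are thin here. Second, Student's t-test pools the two variances. With equal arms it tolerates unequal variances fairly well; with unequal arms its false-positive rate depends on which arm is the more variable. Section 3.2 says the trial is to inform a go/no-go decision on a larger trial, and an imbalance cannot be undone once all 14 have been randomized.

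**Working it through.** **Inputs.** From section 2.9: difference 50 percentage points, SD 30 (the upper end of the stated SD), alpha 0.05, power 80%, 12 evaluable, 14 randomized. From section 2.4: simple randomization, modelled as independent 50:50 draws. Assumption: alpha is two-sided, since sidedness is not stated.

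**1. The plan's own figure.** By the normal approximation, n per arm = 2 × (1.960 + 0.842)² × (30/50)² = 2 × 7.85 × 0.36 = 5.65, rounded up to 6. That is 12 in total, as stated. Inflating for loss, 12 × 1.15 = 13.8, gives 14. (Dividing instead, 12/0.85 = 14.1, would round up to 15; that is not the point here.)

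**2. Arm sizes under simple randomization.** The number on abatacept is Binomial(14, 0.5), so each count is C(14, k)/16,384, doubled for the mirror-image split.

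- 7:7: 3,432/16,384 = 20.9%
- 6:8: 2 × 3,003/16,384 = 36.7%
- 5:9: 2 × 2,002/16,384 = 24.4%
- 4:10: 2 × 1,001/16,384 = 12.2%
- 3:11 or worse: 2 × (364 + 91 + 14 + 1)/16,384 = 5.7%

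Hence P(smaller arm 5 or fewer) = 6,946/16,384 = 42.4%, and P(smaller arm 4 or fewer) = 2,942/16,384 = 18.0%.

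**3. Power with all 14 evaluable.** Noncentral t with 12 degrees of freedom and noncentrality 50 / (30 × √(1/n₁ + 1/n₂)).

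| Split | Noncentrality | Power |
|---|---|---|
| 7:7 | 3.12 | 81.6% |
| 6:8 | 3.09 | 80.8% |
| 5:9 | 2.99 | 78.3% |
| 4:10 | 2.82 | 73.5% |
| 3:11 | 2.56 | 65.2% |

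Weighted by the probabilities in step 2, the average is 78.4%. Against 81.6% at a fixed 7:7, the loss is 3.2 points.

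**4. Power with 12 evaluable.** The t-test gives 74.0% at 6:6 and 72.8% at 5:7. A 7:7 list that loses two participants at random ends at 6:6 with probability 49/91 and at 5:7 with probability 42/91, so its average is 0.538 × 74.0 + 0.462 × 72.8 = 73.4%. Averaged over Binomial(12, 0.5) splits, simple randomization gives 69.9%. The loss is 3.5 points. The fair comparator is 73.4% and not 74.0%, because a balanced list does not guarantee that losses are balanced.

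**5. Type I error when variances differ (illustration).** The article gives no SD for the abatacept arm, so a 2:1 SD ratio is an assumption. Simulated null trials with the pooled t-test at nominal 5% give:

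- 7:7: 5.7%
- 5:9, smaller arm more variable: 10.7%
- 5:9, larger arm more variable: 2.5%
- average over all simple-randomization splits: about 6.5%

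With equal variances the rate stays near 5% at 5:9 and 4:10.

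**The case against.** The strongest reply is that nothing here is invalid. Simple randomization is unbiased and fully unpredictable, and under it 1:1 properly describes the allocation probability and does not promise 7:7. That stands: the sections do not strictly contradict each other.

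A reader might take the 42.4% as the chance that the trial ends up underpowered. The article does not support that. Section 2.9 asks for 12 participants in total and sets no minimum per arm. A 5:9 split with all 14 evaluable has 78.3% power, more than the 74.0% of 6:6, and accounts for 24.4 of the 42.4 points. Even 4:10, at 73.5%, is about level with 6:6. Most of the gap to 80% at 12 evaluable comes from sizing by the normal approximation, which is a separate matter. If the SD is below 30, as section 2.9 expects, power is higher throughout.

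A reader might also infer that the false-positive rate is in fact doubled. That rests on an assumed SD ratio and on the smaller arm being the more variable one. Moreover, if the variances are expected to differ because abatacept suppresses the surge, that reason weakens under the null hypothesis, where the rate is defined. The figures show sensitivity; they are not a forecast.

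Finally, the authors may have used the term loosely, for an unstratified list that was constrained to balance. The full protocol is not shown, so this cannot be confirmed. If so, the sentence in section 2.4 needs correcting.

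**Conclusion.** The point holds in a limited form. As written, section 2.4 does not secure the equal arms that section 2.9 uses: about four lists in five (79.1%) would depart from 7:7. The expected cost is about 3 points of power, with marked loss confined to the 18.0% of lists at 4:10 or worse. There is also some loss of robustness in the pooled t-test, whose size depends on an arm variance that the article does not give. These figures assume independent fair draws, a two-sided test, SD 30, and losses unrelated to arm. This is an avoidable inefficiency, not a flaw that invalidates the trial, and it merits a recommendation, not a mandatory change.

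**What to change.** In section 2.4, replace simple randomization with a restricted list that closes at 7:7, for example randomly permuted blocks of varying size totalling 14, with the block sizes known only to the pharmacist. If enrolment has begun, the restriction can be applied to the remaining allocations. If the existing list was already constrained to balance, correct the wording instead.

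The cost is one sentence and a new list. The statistical downside is a slight loss of unpredictability, negligible in a double-blind, single-centre trial in which the pharmacist generates the list.
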